# Study Protocol for a Randomized Controlled Trial of Low Intensity Shockwave Therapy for the Treatment of Post-Radical Prostatectomy Erectile Dysfunction: “SHARP-ED TRIAL”

**Published:** 2024-04-08

**Keywords:** Clinical trials, Erectile dysfunction, Shockwave therapy, Restorative therapy

## Abstract

**Introduction::**

Erectile Dysfunction (ED) is a common challenge post Radical Prostatectomy (RALP), affecting men’s sexual health after undergoing definitive cancer therapy. Despite employing nerve-sparing techniques, ED remains a prevalent issue in this population. Studies indicate that approximately 70%–85% of men experience varying degrees of ED following RALP. The existing treatment landscape for post-RALP-ED presents limitations, and a discernible knowledge gap persists. To address this, our study aims to investigate the efficacy of Shockwave Therapy (SWT) as a potential intervention for managing ED after RALP.

**Methods::**

This prospective, randomized, sham-controlled clinical trial aims to recruit 189 eligible patients post-RP and assess the effects of SWT. Comprehensive screening, including medical history, physical examinations, and biochemical evaluations, will be conducted to confirm eligibility. The intervention involves utilizing a device to administer focal shockwaves targeted at cavernosal tissue. Safety measures include continuous monitoring for adverse events and rigorous reporting protocols. The primary endpoint assesses changes in participants’ ability to engage in penetrative intercourse from baseline to study completion, while secondary endpoints encompass various measures of erectile function, including questionnaire-based assessments, ultrasound parameters, and clinical outcomes.

**Results::**

Statistical analysis, encompassing ANOVA for continuous variables and Fisher’s exact test for categorical ones, will evaluate demographic characteristics, baseline data, and primary as well as secondary outcomes for statistical significance. Detailed analysis of trends, subgroup comparisons, and treatment effects will provide a comprehensive understanding of the impact of SWT on post-RP ED.

**Conclusion::**

This study protocol represents a rigorous investigation into the potential therapeutic role of SWT in managing post-RP ED. The outcomes from this study aim to contribute valuable insights into the efficacy, safety, and potential improvements in erectile function following SWT, providing significant guidance for future interventions aimed at addressing this challenging condition affecting men’s health and quality of life.

## INTRODUCTION

The surgical procedure of radical prostatectomy is associated with damage to the Cavernous Nerves (CN) and erectile dysfunction. Each year there are approximately 250,000 newly diagnosed cases of Prostate Cancer (PCa) in the United States; overall, it is estimated that 15.3% of all men will be diagnosed with PCa at some point during their lifetime. Radical Prostatectomy (RP) is a common surgical treatment used for localized PCa. Although the long-term oncologic outcome following RP are good, a significant number of patients suffer from post-surgical lower urinary tract complications, including incontinence and ED [1–4]. In most patients, incontinence resolves within 3-months. However, ED may persist for years, and many patients never fully recover erectile function. The prevalence of ED following RALP is a significant concern, with studies indicating a substantial impact on men’s sexual health. Current research suggests that approximately 80% of men may experience varying degrees of ED after undergoing RALP [2], highlighting the high number of men affected by this condition in the post-surgical period. Despite advancements in surgical techniques and the implementation of nerve-sparing approaches, ED remains a prevalent and challenging consequence for a substantial majority of individuals who undergo RALP.

Nerve injury is recognized as a key-factor in the development of post-surgical erectile dysfunction. Even though nerve-sparing techniques are now routinely practiced when performing RP, CN injury, as a result of thermal damage, ischemic injury, mechanically induced nerve stretching and inflammatory effects, remains a major factor in development of ED following surgery. Compounding the acute effects of RP on erectile function, the loss of stimulatory neuronal signals that initiate spontaneous erections results in an overall reduction in oxygenation of erectile tissue, which leads to progressive changes in penile architecture that include induction of smooth muscle apoptosis, fibrosis and deposition of collagen. The effects of long-term ED on penile architecture are such that even when there is CN regeneration, erectile function cannot be fully recovered. Prevention of chronic ED following RP is often considered a race in time between CN regeneration versus irreversible changes in penile architecture.

Accelerating cavernous nerve regeneration has shown potential in improving erectile function outcomes in animal models of radical prostatectomy. Although PDE5 inhibitors represent the first-line oral treatment for ED, their mechanism of action is dependent on the release of nitric oxide from functional CN innervated erectile tissue. Therefore, because of iatrogenic damage to the CN, the vast majority of patients undergoing RP are refractory to treatment of ED by PDE5 inhibitors (PDE5i). In the absence of effective oral treatments for ED, patients that undergo RP are recommended to undergo “penile rehabilitation”. This has a goal of maintaining the erectile tissue oxygenation levels in the acute phase of CN injury to prevent changes in penile architecture, until a time when there is functional CN repair. The strategy commonly utilizes (separately or in combination) intracavernosal injections, vacuum erection devices and low dose PDE5i administration.

The University of Miami “Erectile Preservation Protocol” is used for patients that will undergo a radical prostatectomy. This involves oral PDE5i which treat ED. Patients require additional treatment in order to obtain penetration in roughly 60%–75% of cases [5]. These more invasive treatments involve intracavernosal injections at the time of intercourse. The goal of the study is to have patients involved in penetrative intercourse as rapidly as possible without the use of more invasive treatment options.

The study is aimed at determining the safety and effectiveness of SWT in a patient population soon after? (Maybe even include the number of days to emphasize this is soon after RP) after radical prostatectomy. The rationale behind this is that SWT has been known to bolster angiogenesis and neurogenesis by increasing the levels of vascular endothelial growth factor. The shockwaves are focused onto linear segments that are aimed at the left and right corpora cavernosa and the crura. SWT has previously been shown to improve IIEF scores for organic erectile dysfunction [6]. However, there is a lack of sufficient data on the use of Li-ESWT for penile rehabilitation in the treatment of ED after prostate cancer therapy [7,8]. Existing protocols for SWT are not standardized and involve a limited number of participants with short follow-up periods. Our study aims to evaluate this question using a robust randomized protocol using an adequate number of participants and longitudinal follow up soon after RP.

## MATERIALS AND METHODS

The study adopts a prospective, randomized, sham-controlled clinical trial design to evaluate the safety and efficacy of Shockwave Therapy (SWT) in managing ED post-radical prostatectomy. 189 eligible patients meeting specific inclusion criteria are included and randomly assigned in a 2:1 ratio into either an active treatment group or a sham group. They will be enrolled 6 weeks after their radical prostatectomy to ensure an undetectable PSA. The total duration of the study will be 13 months. This includes pre-treatment screening, 6-months of shockwave therapy sessions, and follow-up at 6-months post treatment.

The comprehensive medical evaluation process includes thorough screening for eligibility, detailed assessment of medical history, comprehensive physical examination, and a battery of blood tests to measure testosterone levels and other relevant biochemical markers. The International Index of Erectile Function (IIEF-EF) questionnaire is employed to assess ED severity and confirm eligibility, while past usage of PDE5 inhibitors is documented.

The SWT intervention utilizes the MoreNova device, directing shockwaves toward specific cavernosal tissue segments. The rationale for utilizing SWT is based on its recognized potential to stimulate angiogenesis and neurogenesis, offering potential in facilitating the recovery of erectile function post-RP.

### Participants

The inclusion criteria are as follows: (i) Be willing and able to provide informed consent; (ii) Be male; (iii) Be ≥ 40 and ≤ 75 years of age (inclusive); (iv) Undergo radical prostatectomy for prostate cancer (nerve sparing or non-nerve sparing without neoadjuvant chemotherapy or radiation therapy.); (v) Be at least six weeks post radical prostatectomy; (vi) Be in a stable sexual relationship for over 3 months prior to enrollment; (vii) Have a serum testosterone level of 300 ng/dL-1000 ng/dL within 1 month prior to enrollment; (viii) Have a HbA1c level ≤ 7% within 3 months prior to enrollment; and (ix) Have undetectable PSA value at the time of enrollment. Patients of all prostate cancer grades/stages and Gleason scores will be included as long as no adjuvant or salvage treatment is needed. Patient drop out will be due to patient preference, adverse effects, cancer recurrence, or need for further cancer treatment.

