### Data analysis

The average and standard deviation of all relevant variables, including demographic and baseline characteristics, primary and secondary outcomes will be calculated. IIEF-EF and EHS scores will be analyzed using ANOVA with repeated measures throughout the study, in order to compare the trends between the treatment and sham group. GAQ, SEP and success rates will be analyzed and compared between the groups according to Fisher’s exact test in each of the endpoints. The statistical significance will be set at P<0.05.

Demographic characteristics such as age and ED duration will be compared between treatment group and sham group using student’s T-Test. Other demographic characteristics, such as medical background and risk factors will be compared between these groups using Fisher’s Exact Test.

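### Pre-operative erectile function is neither a listed entry condition nor scheduled for measurement, so a likely strong prognostic factor goes unused in randomization and in the primary comparison

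*Protocol article*

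**What the plan says.** All references are to the protocol article.

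- **Participants** lists nine inclusion criteria. The surgical one reads "Undergo radical prostatectomy for prostate cancer (nerve sparing or non-nerve sparing without neoadjuvant chemotherapy or radiation therapy". The nearest to sexual function is "Be in a stable sexual relationship for over 3 months prior to enrollment", which does not measure erections. Age runs from 40 to 75.
- **Materials and Methods** sets the timing: "They will be enrolled 6 weeks after their radical prostatectomy to ensure an undetectable PSA". Participants has at least six weeks, with no upper limit listed. The IIEF-EF "questionnaire is employed to assess ED severity and confirm eligibility, while past usage of PDE5 inhibitors is documented"; no cut-off is given.
- **Table 1** schedules the first IIEF-EF at screening, 0 to 30 days before treatment, together with a medical and urological history. It has no pre-operative or recalled IIEF-EF.
- **Data analysis** states that "Demographic characteristics such as age and ED duration will be compared between treatment group and sham group", by t-test. Success rates are compared by Fisher's exact test.
- **Procedures involved** describes computer randomization in a 2:1 ratio and names no strata. It refers to exclusion criteria, which the article does not list.
- The rationale is surgical injury and recovery: "Nerve injury is recognized as a key-factor in the development of post-surgical erectile dysfunction" (Introduction), with shockwaves "offering potential in facilitating the recovery of erectile function post-RP" (Materials and Methods).

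**The concern.** The trial asks whether treatment helps men regain function lost through surgery. How much a man can regain depends on what he had before the operation. A man of 70 who could not have intercourse before prostatectomy and one who could may give the same IIEF-EF soon after it. The baseline score, and any cut-off applied to it, would treat them alike.

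Pre-operative function is therefore likely to be a strong predictor of the primary endpoint, yet the design described does not measure it directly, balance the arms on it or use it in the comparison. Men who are unlikely to succeed in either arm dilute the difference. An uneven split of such men between 63 controls and 126 treated men would move the estimate by chance. If the result were null, the sponsor could not readily tell an ineffective treatment from a diluted one.

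**Working it through.** **Step 1. Is the baseline always post-operative?** Treatment begins 6 weeks (42 days) after surgery, and screening falls up to 30 days before treatment. The earliest screening is then about 42 − 30 = 12 days after the operation. On any reading of the timing, the first IIEF-EF follows surgery.

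**Step 2. What bears on earlier function?** Three items do, all indirectly:
- *Past PDE5i use*: a drug history. It does not grade function.
- *Medical and urological history*: may record earlier ED. No item on it is specified.
- *ED duration*: a duration longer than the time since surgery would mark ED that came first. Its one stated use is a t-test of arm means, which does not adjust the primary comparison.

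**Step 3. Reproduce the plan's sample size.** Inputs from Sample size calculation: 20% v 40%, power 80%, significance level 5% (taken as two-sided), 63 control and 126 active. With pooled variance, no continuity correction and p̄ = (0.20 + 2 × 0.40)/3 = 0.333:

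n(control) = [1.960 × √(1.5 × 0.333 × 0.667) + 0.842 × √(0.20 × 0.80 + 0.40 × 0.60/2)]² / 0.20² = 62.2, rounded up to 63. The total is 3 × 63 = 189, as stated.

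Power = Φ[(d − 1.960 × SE0)/SE1], where d is the difference, SE0 = √[p̄(1 − p̄)(1/63 + 1/126)] = 0.0727 and SE1 = √(0.16/63 + 0.24/126) = 0.0667. This is Φ[(0.20 − 0.1426)/0.0667] = Φ(0.86) = 80.6%. Exact enumeration of the two-sided Fisher test gives 78.8%.

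**Step 4. Illustrate dilution.** The documents give no share of men with prior ED, so the share f is an assumption. Let the planned 20% v 40% hold in the other men. Case A: men with prior ED never succeed. Case B: they succeed at 5% v 10%. Overall rates in case A are (1 − f) × 20% and (1 − f) × 40%; case B adds f × 5% and f × 10%.

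| f | Case A rates | Case A power | Case B rates | Case B power |
|---|---|---|---|---|
| 0 | 20% v 40% | 80.6% | 20% v 40% | 80.6% |
| 10% | 18% v 36% | 73.9% | 18.5% v 37% | 75.7% |
| 20% | 16% v 32% | 66.4% | 17% v 34% | 70.3% |
| 30% | 14% v 28% | 58.1% | 15.5% v 31% | 64.4% |

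If the 20% already describes a mix of this kind, and 40% is the aim for the same mix, the first row applies and nothing is lost against plan.

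**Step 5. Chance imbalance.** The standard error of the difference between arms in the share of such men is √[f(1 − f)(1/63 + 1/126)]. At f = 20% it is 0.062, so without stratification a difference of up to 1.96 × 6.2 = 12 percentage points lies within ordinary chance.

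**Step 6. What stratifying recovers in case A.** A stratum without successes contributes nothing, so the comparison rests on the other (1 − f) × 189 men at 20% v 40%. Both standard errors in Step 3 are divided by √(1 − f). For f = 20%: Φ[(0.20 − 1.960 × 0.0813)/0.0745] = Φ(0.54) = 71%, against 66.4% unstratified. For f = 10% and 30% the figures are 76% and 64%, against 73.9% and 58.1%. Stratifying recovers part of the loss.

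**The case against.** **The information is partly there.** This stands. A reader might infer that nothing in the trial captures earlier ED. The three items in Step 2 of the working show otherwise. They fall short because none grades pre-operative function and none enters the randomization or primary comparison described.

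**The exclusion criteria are not shown.** This also stands. An exclusion for pre-existing ED may sit in the full protocol, so the point is confined to the listed inclusion criteria and the scheduled measurements. If such an exclusion exists, the sponsor can simply confirm it.

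**Comparing ED duration proves that men with prior ED enter.** A reader might infer this by reasoning that surgical ED at a fixed 6 weeks would have almost constant duration. The text does not support it: entry at six weeks or later, with no listed upper limit, lets duration vary in purely surgical ED.

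**Zero response is too harsh, and the 20% may already be diluted.** Both are fair. The Introduction cites benefit of shockwaves in organic ED, and the primary endpoint permits PDE5i, so men with prior ED might respond. The 20% comes from initial observations in patients who are not described further.

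**Broad entry suits the aim.** The discussion wants fewer patients to need invasive treatment, and the trial takes nerve-sparing and non-nerve-sparing cases alike. Restricting entry is a trade-off, and the documents do not make it necessary.

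**Conclusion.** The point holds in a limited form. No listed inclusion criterion sets pre-operative erectile function, no actual or recalled pre-operative IIEF-EF is scheduled, and the post-operative baseline cannot stand in for one. A likely strong prognostic factor is therefore left out of the randomization and the primary comparison as described.

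The consequence is not bias between arms, because randomization balances the factor on average. It is lost precision, possible chance imbalance and a harder reading of a null result. Power of 74% to 58% is an illustration that needs three assumptions: a share of 10% to 30%, no success among these men in either arm, and planned rates that describe only the other men. A reader might take those figures as the trial's real power. The documents do not support that, since they give no share and do not say whom the 20% describes. There is little slack, however: 80.6% is barely above target, and no dropout allowance is stated.

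This is a worthwhile, inexpensive improvement rather than a fault that invalidates the design.

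**What to change.** 1. In Table 1, add to the screening visit a recalled pre-operative IIEF-EF, or one history item on ability to have penetrative intercourse before surgery. It must be completed before randomization.
2. Stratify the computer randomization on it: functional v not functional before surgery.
3. In Data analysis, compare the primary success rates with a stratified or adjusted method, such as Cochran-Mantel-Haenszel or logistic regression, in place of the unadjusted Fisher test.
4. Keep entry broad, and keep ED duration among the characteristics compared, since it carries information about earlier ED.
5. State which men the 20% describes, so that the planned rate can be set against those enrolled.

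The cost is one extra questionnaire or item at an existing visit and one stratum. Recall is imperfect and is likely to worsen with time since surgery. No one is excluded and no visit is added.

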### Interventions

MoreNova is a Linear Shockwave (LISW) device, which incorporates a shockwave transducer operable to deliver shockwaves to a treatment region confined to a narrow rectangle. Shockwaves generation follows the electromagnetic principle. Linear Shockwaves (LISW), as a treatment for ED has been in evaluation in contemporary medicine, it has been in use for the last ten years. The present study will utilize a device called “MoreNova”, in which shockwaves are focused onto linear segments for improved organ coverage. Shockwaves produced by “MoreNova” are aimed at the left and right corpora cavernosa and the crura. The study is aimed at determining the safety and effectiveness of this new type of LISW in the treatment of ED. The rationale behind this is that LISW has been known to bolster angiogenesis and neurogenesis by increasing the levels of vascular endothelial growth factor [9].

### Endpoints

The primary endpoint includes changes in the participant’s ability to have penetrative intercourse (without the use of intracavernosal injections, and with or without PDE5i use) from baseline to study completion. This information will be collected using the IIEF-EF questionnaire. The secondary endpoints are sexual activity improvement leading to optimal penetration at follow-ups which will be done according to: (i) Percentage of participants who achieve Minimal Clinically Important Differences (MCID) in IIEF score based on their ED severity at baseline. This is measured using the Change International Index of Erectile Function (IIEF-EF) Questionnaire score; (ii) Change in median International Index of Erectile Function–Erectile Function subdomain (IIEF-EF) from baseline to each follow-up time point in active therapy recipients compared to placebo; (iii) Change in median Sexual Encounter Profile questions number 2 and 3 from baseline to each follow-up time point in active therapy recipients compared to placebo; (iv) Change in median Global Assessment Questionnaire (GAQ) score from baseline to each follow-up time point in active therapy recipients compared to placebo; (v) Change in median Erection Hardness Scale (EHS) score from baseline to each follow-up time point in active therapy recipients compared to placebo; (vi) Changes in duplex ultrasound parameters from baseline to study completion in active therapy recipients compared to placebo.

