### Follow-up interventions

Follow-up visit will be conducted at 6 months after the last treatment session and shall include: (i) Questionnaires to measure the ability to have penetrative intercourse (IIEF-EF, GAQ, SEP, and EHS); (ii) Recording adverse events; and (iii) Penile Doppler Ultrasound (Table 1).

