### Sample size calculation

In our research protocol, we aim to assess the effectiveness of shockwave therapy on patients’ ability to engage in penetrative intercourse after a one-year period. Our initial observations revealed that 20% of patients achieved this without therapy, whereas an aim of 40% will achieve it with shockwave therapy. To design our study with statistical rigor, we utilized an allocation ratio of 2:1 (control:shockwave), and factored in a power of 80% and a significance level of 5%. Employing calculated Z-values for α and β, we derived an estimated sample size requirement of approximately 189 participants. The overall sample size was determined to be 189 patients, with 63 patients in the control group and 126 in the active treatment group.

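### The primary endpoint is defined as a change from baseline but sized as a one-year proportion, and the listed criteria do not make the two the same

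*Protocol article*

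**What the plan says.** Three sections of the protocol article describe the primary outcome.

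- **Endpoints:** "The primary endpoint includes changes in the participant’s ability to have penetrative intercourse", without intracavernosal injections and "with or without PDE5i use) from baseline to study completion". The IIEF-EF is named as the source. The Abstract and the Results and Discussion section also speak of changes in this ability.
- **Sample size calculation:** the quantity is "patients’ ability to engage in penetrative intercourse after a one-year period", with no baseline term. The rates are given as follows: "Our initial observations revealed that 20% of patients achieved this without therapy, whereas an aim of 40% will achieve it with shockwave therapy".
- **Data analysis:** "GAQ, SEP and success rates will be analyzed and compared between the groups according to Fisher’s exact test in each of the endpoints". Success is not defined, no time point is attached to it, and baseline does not enter.

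On who can enter, the nine inclusion criteria under Participants contain no requirement of erectile dysfunction, IIEF-EF cut-off or inability to penetrate. Nerve-sparing and non-nerve-sparing surgery both qualify. Materials and Methods says that the IIEF-EF helps to confirm eligibility but gives no threshold. The Introduction says that roughly 60% to 75% of patients on the institution's PDE5 inhibitor protocol need further treatment to achieve penetration, without giving a time point.

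**The concern.** A change in ability and ability at the end are the same outcome only if every man is unable at the start. A man able at both times is a success on one definition and shows no change on the other. The listed criteria do not exclude such men. The Introduction's figure implies that about 25% to 40% (100% minus 75%, and 100% minus 60%) manage penetration with oral treatment alone at some unstated time, so ability at baseline is at least possible.

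Two things are at stake. First, two primary outcomes are open, and the choice between them could be made after the data are seen. Second, the 80% power is attached to a pair of rates whose meaning is not fixed, so the real power of the primary test is unknown.

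**Working it through.** **Inputs.** From Sample size calculation: control 20%, active 40%, power 80%, significance level 5% (sidedness not stated), 63 control and 126 active. Assumption, because the documents give no figure: a share b of men is able at baseline, equal in both arms by randomisation, and stays able.

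**Step 1: reproduce the plan's figure.** Take the pooled formula for two independent proportions, two-sided, with k = 2 active men per control:

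n(control) = [1.96 × √((1 + 1/k) × p̄(1 − p̄)) + 0.842 × √(p1(1 − p1) + p2(1 − p2)/k)]² / (p2 − p1)²

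Here p̄ = (0.20 + 2 × 0.40)/3 = 0.333. This gives (1.96 × 0.577 + 0.842 × 0.529)² / 0.04 = 62.2, rounded up to 63 control and 126 active, 189 in total. The match is exact, so the sizing treats the primary as a plain proportion. Power at 63 v 126 is 0.806 by this formula and 0.788 for Fisher's exact test, the test that the plan names.

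**Step 2: two meanings of 20%/40%.**

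*Reading A: one-year rates in all men.* 'Able at Month 12' stays at 20% v 40%. 'Became able' is (20% − b) v (40% − b).

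*Reading B: gain rates in men unable at baseline.* 'Able at Month 12' is b + (1 − b) × p. 'Became able' is (1 − b) × p.

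Exact Fisher power at 63 v 126:

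| Reading | b | Able at Month 12 | Power | Became able | Power |
|---|---|---|---|---|---|
| A or B | 0% | 20% v 40% | 0.79 | 20% v 40% | 0.79 |
| A | 5% | 20% v 40% | 0.79 | 15% v 35% | 0.84 |
| A | 10% | 20% v 40% | 0.79 | 10% v 30% | 0.89 |
| A | 15% | 20% v 40% | 0.79 | 5% v 25% | 0.96 |
| B | 10% | 28% v 46% | 0.64 | 18% v 36% | 0.73 |
| B | 20% | 36% v 52% | 0.53 | 16% v 32% | 0.65 |

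**Step 3: the effect size.** Within each row the risk difference is the same under both definitions. At b = 10% it is 20 points under A (40 − 20 and 30 − 10) and 18 points under B (46 − 28 and 36 − 18). The definitions change the rates and the power, not the expected difference.

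**Step 4: using the baseline value.** If men able at baseline stay able, their stratum carries no information on treatment. A test stratified by baseline ability is then roughly a test among the men unable at entry. At b = 10% there are 63 × 0.9 ≈ 57 and 126 × 0.9 ≈ 113 of them.

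- Reading A: their rates are (0.20 − 0.10)/0.90 = 11.1% and (0.40 − 0.10)/0.90 = 33.3%. Power is about 0.90, against 0.79 for the unadjusted Month 12 test.
- Reading B: 20% v 40%. Power is about 0.74, against 0.64.

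At b = 20% under reading B (50 v 101 men), power is about 0.69, against 0.53.

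**The case against.** **Power.** A reader might infer that the trial is underpowered because men already able dilute the Month 12 comparison. The documents do not support that as a fact. Taken literally, the sample size section gives one-year rates among patients generally (reading A). The Month 12 test then keeps its planned power whatever the baseline share, and 'became able' has more. The dilution appears only under reading B, which the text does not state. This objection stands: the direction of the effect is open.

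**Bias.** Under randomisation the expected difference between arms is the same on both definitions if men able at baseline stay able. This also stands. The harm is an unfixed primary and uncertain power, not a distorted effect.

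**Entry criteria.** The full protocol may require inability. The article mentions exclusion criteria without listing them, uses the IIEF-EF to confirm eligibility, and compares duration of erectile dysfunction between the groups, which suggests that all men have it. The Introduction also calls the vast majority of men refractory to PDE5 inhibitors after surgery. So the baseline share may be small or nil. Even then, the wording of the endpoint and of the sizing would still need aligning.

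**The test.** One might say that the plan tests a plain one-year proportion. That is only partly on the page, because success is undefined and could equally mean unable to able. An unadjusted Fisher test on a randomised binary outcome is valid, so the adjustment proposed below is an improvement and not the correction of an error.

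**The source.** A reader might see a further conflict in Follow-up interventions, which lists "Questionnaires to measure the ability to have penetrative intercourse (IIEF-EF, GAQ, SEP, and EHS"). That section only lists the instruments given at the visit. The Endpoints section assigns the primary to the IIEF-EF, so there is no contradiction.

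**Conclusion.** The inconsistency is real. The protocol article defines its primary as a change from baseline, sizes it as a one-year proportion and tests a success rate that it does not define. The 189 is not an arithmetic error; it reproduces exactly for two plain proportions.

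The size of the consequence rests on two things that the documents do not give: the share of men able at baseline, and whether 20%/40% are rates in all men or gains among men unable at entry. At an assumed 10% share, with able men staying able, Fisher power runs from 0.64 to 0.89 across the four combinations of definition and reading. At a zero share all four are 0.79. It cannot be said that 80% power will be missed, only that the text does not settle whether it will be met. This should be corrected before the analysis is fixed.

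**What to change.** 1. State one primary: the proportion of all randomised men able to have penetrative intercourse without intracavernosal injection at Visit 11 (Month 12), as a single yes/no derived from the IIEF-EF, which the Endpoints section already names.
2. Use that definition in Endpoints, Sample size calculation and Data analysis, and state that 20% and 40% refer to it.
3. For the primary, replace the unadjusted Fisher test with a test stratified by baseline ability, or a logistic regression adjusted for it, taking baseline ability from the screening IIEF-EF.
4. Report 'became able' as a secondary outcome.

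The cost is wording in the protocol and analysis plan. Table 1 already schedules the IIEF-EF at screening and at Month 12, so no visit or data item is added. If 20%/40% are one-year rates in all men, 189 stands. If the sponsor finds that they were gain rates among men unable at entry, the sizing needs another look. On that reading the unadjusted Month 12 comparison would need 219, 255 or 339 men for 80% power at baseline shares of 5%, 10% or 20% (same pooled formula), and the adjustment in item 3 recovers part of that loss.
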